Despite great interest, due to lack of availability of clinical evidence for the safety and efficacy of hyperimmune IVIG in COVID-19 patients, the use of hyperimmune intravenous immunoglobulin as one of the first-line therapeutic options against COVID-19 has been limited. In this context, an adaptive phase II/III, multicenter center, single-blinded superiority trial has been designed to assess the safety and efficacy of single dose of hyperimmune anti-COVID-19 intravenous immunoglobulin (C-IVIG) in severe COVID-19 patients after observing safety and efficacy of C-IVIG in phase I/II clinical trial of severe and critical COVID-19 patients [11].

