#### Sample size {14}

Three hundred nine participants will be enrolled in the study. Sample size was determined by taking proportion of survival in intervention group (P1) = 75%, proportion of survival in control group (P2) = 40%, power of test (1-β) = 90%, with the sample ratio 2:1 (test to control), superiority margin 0.15, and drop rate 30%. The calculated total sample size is 309 patients, 206 tests and 103 control. The calculated sample size was determined with the help of online sample size calculator (www.riskcalc.org) taking 99% confidence level (11).

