### Statistical methods

#### Statistical methods for primary and secondary outcomes {20a}

Patients will be randomized at a ratio of 2:1 to receive either C-IVIG with standard of care or standard of care only. The data to be analyzed will be blinded using the SPSS software 24.0. All randomized study participants will be included in the intention-to-treat population and all participants completing the study period will be analyzed (complete case analysis). Normality of continuous data will be checked by the Shapiro-Wilk test, and parametric or non-parametric tests will be applied accordingly. Continuous variables will be presented as mean (± SD) or median (interquartile range), and categorical variables will be presented as percentages. In the primary analysis strategy, we will use the Kaplan–Meier curve (Breslow test) that compares the time to reach the primary end point in the trial groups. Hypothesis testing of outcomes for the assessment of safety and efficacy parameters will be conducted by Mann-Whitney *U* test or independent *t*-test. Categorical data will be compared with chi-square test, and value of the two-sided Fisher exact test will be recorded. An estimate of the relative risk and 95% confidence interval will also be reported. Hypothesis testing will be conducted at a significance level of 0.05.

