## Discussion

This phase II/III clinical trial is an adaptive, randomized controlled, multi-center, single-blinded superiority trial of SARS-CoV-2 specific polyclonal IVIG (C-IVIG) versus standard of care for patients hospitalized with severe COVID-19. Single dose of C-IVIG in combination with the standard of care was found to be both safe and efficacious in our previous clinical trial phase I/II while increasing the survival rate and reducing the risk of disease progression [13]. There were no significant changes observed when different doses of C-IVIG were compared in the phase I/II; however, it was found that C-IVIG dosage of 0.15 g/kg have significantly improved the therapeutic response in severe COVID-19 patients. These results warrant the phase II/III clinical trial study of C-IVIG, in order to evaluate its safety and efficacy in large sample size by comparing outcomes (28-mortality, hospital stay and drug-related adverse events) of C-IVIG along with SOC in intervention group and SOC only in comparator group provided during the hospital stay.

Study participant selection for this study is based on the results of our previous clinical trial where severe patients had 100% survivability and early hospital discharge than critical patients and comparator group. We evaluated that hospital stay, reliance on mechanical ventilation, and burden on hospital could be reduced if C-IVIG is administered to the severe COVID-19 patients by delaying the disease progression.

This is an adaptive clinical trial to investigate the risk-benefit analysis of C-IVIG administration for severe COVID-19 at first and second interim of the study. Major outcome variables to be assessed for interim analysis are adverse events, 28-day mortality, and change in clinical status of the patients. Fate of this clinical trial is based on whether the C-IVIG is safe and efficacious. If the treatment modality is found to be safe but not efficacious as compare to comparator group, we might select different dosage of C-IVIG for further study participants; if interim analysis indicate association of serious adverse events with administration of C-IVIG or with significant high mortality ratio in intervention group than comparator group or if incidence rate of COVID-19 is low till the study completion date, then this clinical trial would be early terminated due to aforementioned reasons.

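### The 309 patients do not follow from the stated 99% confidence level, which also conflicts with the 0.05 level set for the analysis

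*Protocol article*

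**What the plan says.** The Sample size section {14} of the protocol article lists every input. Survival is given as "proportion of survival in intervention group (P1) = 75" per cent and "proportion of survival in control group (P2) = 40" per cent, and power as "power of test (1-β) = 90" per cent. Allocation is two test patients to one control, the superiority margin is 0.15 and the drop rate is 30%. The result is "The calculated total sample size is 309 patients, 206 tests and 103 control". The section adds that an online calculator was used, "taking 99% confidence level (11").

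The section on statistical methods for primary and secondary outcomes {20a} sets a different level: "Hypothesis testing will be conducted at a significance level of 0.05". It names a Kaplan–Meier comparison with the Breslow test as the primary strategy. It also plans chi-square and two-sided Fisher exact tests for categorical data, and a relative risk with a 95% confidence interval. It does not mention the 0.15 margin.

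**The concern.** A sample size statement is a claim about error rates: this many patients, at this significance level, give this power. Here all the inputs are printed, so the claim can be checked directly, and at the printed level it fails. The level also disagrees with the one set for the analysis.

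A reader or regulator who takes the section at its word believes that a mortality trial was sized for a 1% error rate with 90% power to beat a 15-point margin. Both cannot be true at 309 patients. The disagreement is between two statements in the same article, so it cannot be put down to detail left to an analysis plan that is not shown.

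**Working it through.** **Inputs, all from Sample size {14}.** P1 = 0.75, P2 = 0.40, margin 0.15, power 90% (z = 1.2816), two test patients per control, 30% dropout. The sidedness of the 99% level is not stated, so both readings are tried.

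**Formula.** For superiority by a margin with two proportions and unpooled variance:

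n(control) = (z_α + 1.2816)² × [0.75×0.25/2 + 0.40×0.60] / (0.35 − 0.15)²
= (z_α + 1.2816)² × 0.33375 / 0.04

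Round up, take twice as many for the test arm, divide each arm by 0.70, and round up again.

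**Reproducing the stated figure.** At one-sided 5%, z_α = 1.645 and n(control) = 71.45, so 72. Then 72/0.70 gives 103 and 144/0.70 gives 206, a total of 309. Both arms match exactly.

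**The same inputs at other levels:**

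| Level | z_α | Control, evaluable | Enrolled (test + control) | Total |
|---|---|---|---|---|
| One-sided 5% | 1.645 | 72 | 206 + 103 | 309 |
| Two-sided 5% | 1.960 | 88 | 252 + 126 | 378 |
| One-sided 1% | 2.326 | 109 | 312 + 156 | 468 |
| Two-sided 1% | 2.576 | 125 | 358 + 179 | 537 |

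A 99% level therefore needs 468/309 = 1.51 to 537/309 = 1.74 times the stated number.

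**Is it only the choice of formula?** With pooled variance, 90% power, the margin and dropout, the 1% totals are 489 to 516 (one-sided) and 558 to 588 (two-sided). Without the margin, but with dropout as n/(1 − d), they fall to 156 to 198. With the margin but no dropout allowance, the unpooled totals are 327 and 375. None of these gives 309.

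**Power delivered by 309.** After 30% dropout there are 144 test and 72 control patients:

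SE = √(0.1875/144 + 0.24/72) = 0.0681

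Power against the margin = Φ(0.20/SE − z_α) = Φ(2.938 − z_α)
Power for any difference = Φ(0.35/SE − z_α) = Φ(5.141 − z_α)

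| Level | Against margin, 144/72 | Against margin, no dropout (206/103) | Any difference, 144/72 |
|---|---|---|---|
| One-sided 5% | 90.2% | 96.9% | >99.9% |
| Two-sided 5% | 83.6% | 94.0% | 99.9% |
| One-sided 1% | 73.0% | 88.2% | 99.8% |
| Two-sided 1% | 64.1% | 82.6% | 99.5% |

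Even if nobody drops out, the 1% level does not reach 90% against the margin.

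**The case against.** **The power shortfall belongs to a test the analysis section does not plan.** The 64% to 73% is power to exceed a 0.15 margin. The methods section names the Breslow test, chi-square or Fisher tests and a relative risk, none of them against a margin. For a plain difference at 75% against 40%, power is above 99% even at two-sided 1%. This stands. A reader might infer that the trial is underpowered for its planned comparison, and the article does not support that. It does not rescue the sample size section, though, because that section lists the margin among the inputs to its 90%.

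**The one-sided 5% origin is an inference.** This also stands. No section states it, and the calculator output is not shown. Other routes reach 309. One uses a pooled variance from the simple mean of the two proportions at one-sided 5%, with dropout added as n × 1.3. Another uses the same variance at two-sided 5% with 80% power and division by 0.70. None of these uses a 99% level.

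**How many levels conflict.** It is tempting to count three. Only two are printed, 99% and 0.05; the two-sided Fisher test and the 95% interval agree with 0.05.

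**The survival inputs.** A reader might go further and conclude that 75% and 40% are wrong for this population. The earlier work is described as a "phase I/II clinical trial of severe and critical COVID-19 patients", while this trial excludes critical disease, and the Discussion reports that "severe patients had 100% survivability and early hospital discharge than critical patients and comparator group". That does not establish an error. The reference number is attached to the calculator sentence, and the text does not say that the two survival rates came from that trial. No survival rate is given for severe control patients alone. If survival on treatment were 100%, an assumed 75% would be cautious for that arm.

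**Conclusion.** The sample size statement is wrong as written. At the stated 99% level its own inputs require 468 or 537 patients, against 309 stated. With 309 enrolled, power against the margin is about 73% (one-sided) or 64% (two-sided) after full dropout, and 88% or 83% with none. The 99% level also contradicts the 0.05 level of the analysis section, which in addition does not carry the margin forward.

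The conclusion is limited to the reported level, the reported power and the hypothesis they refer to. It rests on a normal approximation for a difference in 28-day survival proportions, with unpooled variance and no allowance for the interim looks. It does not give the power of the Breslow test. Pooled variance changes the 1% figures after dropout only slightly, to about 71% and 62%.

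**What to change.** Keep 309 and reword the paragraph:

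1. Remove the statement that a 99% confidence level was used.
2. Re-run the calculation and report the level and sidedness actually used. One-sided 5% is the simplest match, but the sponsor should confirm it from the calculator record before printing it.
3. Restate power at the two-sided 0.05 level of the analysis section: about 84% if success means exceeding the 0.15 margin, and above 99% if it means any difference, both at 75% against 40% with 144 and 72 evaluable.
4. Say in both sections which of these hypotheses the primary analysis tests.

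The cost is the rewording and one repeated calculation, with no extra patients. The downside is that the stated confidence level, and the power if the margin is kept, become less favourable. Holding 90% against the margin at two-sided 0.05 would instead take 378 patients, 69 more than planned; the correction does not require this.

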#### Recruitment {15}

Patients will be recruited from Dow University Hospital, and Sindh Infectious Disease Hospital who will be hospitalized with severe COVID-19 pneumonia.

### Assignment of interventions: allocation

#### Sequence generation {16a}

Randomization will be stratified by site and will be in permuted blocks and the randomized sequence allocation will only be accessible to the site investigator. The randomization schedule will be generated by an independent statistician.

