#### Concealment mechanism {16b}

Eligible participants are randomly assigned in 2:1 ratio (206 tests to 103 controls) by sequentially numbered opaque sealed envelopes using block randomization method, either to receive C-IVIG plus SOC (intervention group) or only SOC (control group). A randomization list is generated by a statistician unrelated to this study, while the study personnel will be unaware of the sequence of assignments. At the time of randomization, the study personnel will receive a sealed opaque envelope with assignment to intervention or control group.

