#### Implementation {16c}

Participants will be enrolled by the clinical research associate or by treating physicians of each study site. Participants will be assigned to interventions by investigators according to a randomization list.

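### The protocol gives the site investigator access to the allocation sequence, contradicting its own sealed-envelope procedure, so allocation concealment as written is not secured

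*Protocol article*

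**What the plan says.** Three adjoining sections of the protocol article describe allocation.

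- **Sequence generation {16a}:** "Randomization will be stratified by site and will be in permuted blocks". On who makes the schedule: "The randomization schedule will be generated by an independent statistician". On who may see it: "the randomized sequence allocation will only be accessible to the site investigator". No time limit is attached, such as access only after assignment.
- **Concealment mechanism {16b}:** allocation is made "by sequentially numbered opaque sealed envelopes using block randomization method", from a list produced by a statistician unconnected with the study. On knowledge of the order: "the study personnel will be unaware of the sequence of assignments". Staff receive the sealed envelope at the time of randomization.
- **Implementation {16c}:** "Participants will be enrolled by the clinical research associate or by treating physicians of each study site". Then: "Participants will be assigned to interventions by investigators according to a randomization list". The envelope is not mentioned here.

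Who will be blinded {17a} names participants only, and the section on collection of outcomes {18a} has study investigators collect baseline and outcome data.

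**The concern.** An opaque envelope conceals nothing from a person who can read the list behind it. Someone at a recruiting site who knows the next assignment can delay, bring forward or decline a patient according to prognosis. Eligibility leaves room for this, because oxygen requirement may range from 5 to 15 L.

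The primary outcome, 28-day all-cause mortality, is objective. That protects against biased assessment but not against arms that differ at entry. The planned Kaplan–Meier comparison with the Breslow test and the chi-square comparison do not adjust for prognosis. The interim looks can lead to a change of dose or to early termination, and they would use the same data.

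**Working it through.** **1. The sections side by side.** No figure in the article is at issue, so the main check is one of reading.

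| Question | {16a} | {16b} | {16c} |
|---|---|---|---|
| Who makes the list? | Independent statistician | Statistician outside the study | Not stated |
| Who can see the sequence? | Site investigator only | Study personnel cannot | Not stated |
| How is a patient assigned? | Not stated | Sealed envelope received at randomization | By investigators, from a list |
| Who enrols? | Not stated | Not stated | Research associate or treating physician |

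The first row agrees. The second conflicts directly between {16a} and {16b}. The third can be reconciled if the list in {16c} is the one from which the envelopes were filled, but {16c} does not say so and therefore does not decide which of the other two sections governs.

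**2. What access to the list changes.** The planned split is 206/103 = 2.0, so always guessing C-IVIG is right 2/3 = 66.7% of the time. With t test and c control places left in a block, the best guess is right with probability max(t, c)/(t + c), averaged over all orders. Block size is not given in the article, so the sizes below are assumptions, as is knowledge of the size and of past assignments.

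- Block of 3: the first guess is right with probability 2/3; the second with (2/3 × 1/2) + (1/3 × 1) = 2/3; the third with 1. The mean is (7/3)/3 = 77.8%.
- By the same recursion, a block of 6 gives 74.4%, 9 gives 72.8% and 12 gives 71.7%.
- With the list: 100%.

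**3. Possible size of the bias (illustration; every input is assumed).** Let a share p of an arm be good-prognosis patients with 20% mortality and the rest have 50%. Arm mortality is 0.20p + 0.50(1 − p), so the difference between arms with no drug effect is 0.30 × (p in C-IVIG − p in control). Half of the eligible pool is taken as good-prognosis, so at 2:1 the two shares must satisfy (2 × p in C-IVIG + p in control)/3 = 0.50.

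- No steering: both shares 0.50, difference 0.
- Modest steering, shares 0.55 and 0.40, where (2 × 0.55 + 0.40)/3 = 0.50. C-IVIG: 0.55 × 0.20 + 0.45 × 0.50 = 0.335. Control: 0.40 × 0.20 + 0.60 × 0.50 = 0.380. Difference 4.5 points.
- Arithmetic ceiling, shares 0.75 and 0, where (2 × 0.75 + 0)/3 = 0.50. C-IVIG: 0.75 × 0.20 + 0.25 × 0.50 = 0.275. Control: 0.500. Difference 22.5 points. This is a bound, not a plausible case.

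For scale, the Sample size section plans on survival of 75% against 40%, a 35-point difference, with a margin of 15 points. Steering in the other direction would reverse the sign.

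**The case against.** The strongest reply is that {16b} describes sound concealment: an outside statistician, numbered opaque envelopes and staff unaware of the order. On that view the sentence in {16a} is loose drafting. A reader might infer from {16a} and {16c} that allocation is not concealed in this trial. The documents do not support that. They contain a contradiction and no account of what was done.

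Three further points stand. Assigning from a list is compatible with envelopes made up from that list, so {16c} is ambiguous and not a second clear contradiction. {16c} gives enrolment to the research associate or treating physicians and assignment to investigators; nothing says that the site investigator screens or enrols, so the route to bias needs that person to enrol or to influence those who do. And the illustration rests on invented inputs that differ from the protocol's own planning figure of 60% control mortality (100% − 40% survival).

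The section on statistical methods {20a} also says that the analysed data will be blinded. That acts after assignment and gives no protection at entry.

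What the reply does not remove is the conflict between {16a} and {16b}. The article addresses all three allocation items and answers them incompatibly, so this is not detail left to a fuller document.

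**Conclusion.** The point holds as a contradiction: {16a} opens the sequence to a person at the recruiting site, {16b} says that study personnel do not know it, and {16c} does not resolve the two. Concealment as written is not secured, and the access rule in {16a} is wrong as it stands.

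Bias in 28-day mortality is conditional on the site investigator enrolling patients or influencing enrolment, which the article neither states nor excludes. Adjustment for measured baseline factors would repair such bias only in part, since unmeasured prognosis would remain. No size can be derived from the article. The 4.5-point figure shows the mechanism under assumed inputs and is not an estimate for this trial.

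**What to change.** 1. In Sequence generation {16a}, state that the independent statistician alone holds the sequence, and that no site investigator, treating physician or research associate can see upcoming assignments.
2. In Implementation {16c}, replace assignment from a list by opening the next sequentially numbered opaque envelope, after eligibility and consent have been recorded.
3. State who has actually had access to the list since recruitment began. Trial status gives a start date of August 1, 2021, and the Abstract cites case counts to January 17, 2022, so patients may already have been randomized. New wording cannot protect them. If practice always followed {16b}, only the text needs correcting; if it followed {16a}, that has to be disclosed and weighed when the mortality result is interpreted.

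The cost is a small amendment, which under the section on protocol amendments {25} is implemented only after approval by the authorities, and someone outside enrolment to prepare the envelopes. The statistician and the envelopes are already part of the plan.

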#### Concealment mechanism {16b}

Eligible participants are randomly assigned in 2:1 ratio (206 tests to 103 controls) by sequentially numbered opaque sealed envelopes using block randomization method, either to receive C-IVIG plus SOC (intervention group) or only SOC (control group). A randomization list is generated by a statistician unrelated to this study, while the study personnel will be unaware of the sequence of assignments. At the time of randomization, the study personnel will receive a sealed opaque envelope with assignment to intervention or control group.

#### Implementation {16c}

Participants will be enrolled by the clinical research associate or by treating physicians of each study site. Participants will be assigned to interventions by investigators according to a randomization list.

### Assignment of interventions: blinding

#### Who will be blinded {17a}

This is a single-blinded trial in which trial participants are blinded.

#### Procedure for unblinding if needed {17b}

Unblinding is not needed because the trial is single blinded and only patients will be blinded. Unblinding will only be permissible by study investigators when patient selects to leave against the medical advice (LAMA) to seek treatment in another hospital and the information is important for the safe management of the patient.

### Data collection and management

#### Plans for assessment and collection of outcomes {18a}

Outcome, baseline, and other trial data will be collected by the study investigators. The clinical research associate will check the data. Nasopharyngeal/oropharyngeal swabs and blood samples will be sent to DUHS laboratory, where tests will be performed according to laboratory standard operating procedures (SOPs). Data reports can be found on HMIS (Hospital Management information system) and will be collected on clinical research forms (CRF).

#### Plans to promote participant retention and complete follow-up {18b}

Designated personnel from the trial staff will be appointed to ensure the participant retention and complete follow-up during the participant’s hospital stay and after discharge as well. After a participant’s hospital discharge, participants will be followed on call. The participant can withdraw from the trial at any point. The decision will be communicated with the study investigator; the clinical research associate should be explaining the importance of staying in the trial for the full duration of follow-up. For withdrawal, there is a form in CRF that will be filled by the clinical research associate with reasoning why the participant is withdrawing from the trial. If the participant will be lost to follow-up, the data that will be collected till the time of loss to follow-up will be assessed and used in the analysis.

If the patient will withdraw due to AEs, the clinical associate or the treating physicians will closely monitor the follow-up of AEs until the participants return to the baseline state or the participant condition returns to normal. Then the AEs will be reported to the study investigators.

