#### Criteria for discontinuing or modifying allocated interventions {11b}

Modification of the allocated intervention will be based on the planned interim analysis. Outcome of the interim analysis will lead to making decision regarding selection of higher C-IVIG dose in case of currently selected 0.15 g/kg dose not found efficacious. The higher dose of C-IVIG will be selected from the dosage investigated in previous phase I/II clinical trial [11]. The C-IVIG infusion will be discontinued if any serious adverse event occurs or discontinued on patient request and the patient will be excluded from the study.

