#### Outcomes {12}

Primary outcome:28-day mortality [time frame: 28 days]All-cause mortality of participants will be monitored for 28 days to assess the safety and efficacy of C-IVIG

Secondary outcomes:Immediate (within 24 h) or serious adverse events (throughout the hospital stay) [time frame: 28 days]Clinical status according to 7 category ordinal Scale [time frame: 28 days (till hospital stay)Not hospitalized and no limitations of activitiesNot hospitalized, with limitation of activities, home oxygen requirement, or bothHospitalized, not requiring supplemental oxygenHospitalized, requiring any supplemental oxygenHospitalized, requiring noninvasive ventilation or use of high-flow oxygen devicesHospitalized, receiving invasive mechanical ventilationDeathChange in Horowitz index (PaO_2_/FiO_2_ ratio use to assess lung function) during hospital stay [time frame: 28 days]Change in C-reactive protein (CRP) levels, radiological findings, IL-6 level, and anti-SARS-CoV-2 antibody levels [time frame: 5 days]

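### The rules for withdrawal and for a stopped infusion do not secure day-28 vital status, which is the primary endpoint

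*Protocol article*

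**What the plan says.** Protocol article, Outcomes {12}, sets the target: "All-cause mortality of participants will be monitored for 28 days".

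The rules for patients who depart from the planned course are spread over several sections:

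- **Withdrawal** (retention and follow-up, {18b}): a CRF form is completed "with reasoning why the participant is withdrawing from the trial". If the cause is an adverse event, staff will "closely monitor the follow-up of AEs until the participants return to the baseline state", or until the patient's condition is normal again.
- **Stopped infusion** (discontinuing or modifying interventions, {11b}): the C-IVIG infusion stops for a serious adverse event, or is "discontinued on patient request and the patient will be excluded from the study".
- **Discharge** ({18b}): staff are appointed to achieve complete follow-up in hospital and afterwards, and once discharged "participants will be followed on call".
- **Loss to follow-up** ({18b}): "the data that will be collected till the time of loss to follow-up will be assessed and used in the analysis".
- **Leaving against medical advice** (unblinding, {17b}): unblinding is allowed "when patient selects to leave against the medical advice (LAMA) to seek treatment in another hospital" and the information matters for safe care. Nothing is said about outcome follow-up.

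The statistical methods section {20a} places all randomised patients in the intention-to-treat population and, in the same sentence, describes a complete-case analysis of those who finish the study period. The missing-data section {20c} leaves open multiple imputation or complete cases. The sample size section {14} allows for a 30% drop rate.

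**The concern.** The endpoint is defined for every participant. The specific rules for withdrawal and for a stopped infusion, however, name other things to collect, or remove the patient altogether. Neither states that survival at day 28 will still be sought.

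Two features make this more than a matter of wording. First, the exclusion in {11b} is tied to the C-IVIG infusion, which controls do not receive, so it can remove patients from one arm only. Serious adverse events are one of its triggers, and those patients are plausibly not a random sample. Second, only participants are blinded ({17a}), so staff knowledge of the arm could influence who leaves.

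Data come from the trial sites' own hospital system and files ({19}). A death elsewhere would not ordinarily appear there, which leaves a telephone call as the obvious source. If such deaths go unrecorded more often in one arm, 28-day mortality is biased, and no analysis method can restore a death that could have been ascertained.

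**Working it through.** **Step 1. The plan's own sample size, to see how the 30% enters.** Inputs from {14}: survival 0.75 and 0.40, margin 0.15, power 90%, ratio 2:1, drop rate 30%.

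n(control) = (z_alpha + z_power)² × [0.40×0.60 + 0.75×0.25/2] / (0.35 − 0.15)²

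With one-sided alpha 0.05: (1.64485 + 1.28155)² × 0.33375 / 0.04 = 71.45, rounded up to 72. Then 72/0.70 = 102.9, rounded up to 103 controls; 2×103 = 206 C-IVIG; total 309. The plan's figure is reproduced, and the 30% enters as patients not available for analysis. (The stated 99% level does not give 309: it gives 468 one-sided or 537 two-sided. That is a separate matter.)

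**Step 2. Patients whose survival could be unknown**, if the whole allowance were used that way: 0.30×206 = 61.8, about 62 C-IVIG; 0.30×103 = 30.9, about 31 controls; together 92.7, about 93.

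**Step 3. What unknown survival does to the result.** Suppose the planned survival rates (0.75 v 0.40) are seen among patients with known outcome, with fraction d unknown in each arm.

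- Lower bound = (1−d)×0.75 − [(1−d)×0.40 + d]
- Upper bound = (1−d)×0.75 + d − (1−d)×0.40

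d = 0.30: 0.525 − 0.580 = −0.055 and 0.825 − 0.280 = 0.545, a span of 60 points that includes the 0.15 margin.

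d = 0.05 (assumed, if vital status is sought for everyone): 0.7125 − 0.43 = 0.2825 and 0.7625 − 0.38 = 0.3825, wholly above the margin.

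These are extreme cases, not forecasts.

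**Step 4. Bias with no true effect, analysing only those who stay.** Assumptions: the same true mortality M in both arms, 20% of controls and 10% of C-IVIG patients leaving with unknown survival, and mortality L among leavers. Mortality seen in stayers = (M − p×L)/(1 − p), where p is the leaving rate.

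| M | L | Control, p = 0.20 | C-IVIG, p = 0.10 | False difference |
|---|---|---|---|---|
| 60% | 70% | (60−14)/0.8 = 57.5% | (60−7)/0.9 = 58.9% | 1.4 points |
| 60% | 90% | (60−18)/0.8 = 52.5% | (60−9)/0.9 = 56.7% | 4.2 points |
| 40% | 70% | (40−14)/0.8 = 32.5% | (40−7)/0.9 = 36.7% | 4.2 points |
| 40% | 90% | (40−18)/0.8 = 27.5% | (40−9)/0.9 = 34.4% | 6.9 points |
| 25% | 70% | (25−14)/0.8 = 13.8% | (25−7)/0.9 = 20.0% | 6.3 points |
| 25% | 90% | (25−18)/0.8 = 8.8% | (25−9)/0.9 = 17.8% | 9.0 points |

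The 60% and 25% rows use the mortality implied by {14} for control and C-IVIG (100−40 and 100−75); 40% is an intermediate assumption. As set out, the bias disfavours C-IVIG. Swapping the leaving rates reverses the sign.

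**Step 5. Effect on the test.** Assume survival of 60% in both arms, and that only patients who would die leave, a share q of them. Survival seen = 0.60/[0.60 + 0.40×(1−q)]. With q = 0.30 for C-IVIG and 0.10 for control: 0.60/0.88 = 68.2% v 0.60/0.96 = 62.5%. A two-sided 0.05 comparison of proportions then rejects about 16% of the time (normal approximation). At 20% v 10% the rate is about 7.5%; at equal shares it stays at 5%.

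**The case against.** The strongest counter-argument is that this reads silence in a condensed article. The protocol does monitor death to day 28, appoints staff for complete follow-up, phones discharged patients and records adverse events to day 28 ({22}). The schedule table and the withdrawal form are not reproduced, and a full protocol is said to exist. The treatment is a single dose, so withdrawal from the trial may often mean withdrawn consent, which no rule can override. These points stand as limits. They do not remove the concern, because the article itself states the withdrawal and exclusion rules, and the exclusion works against the endpoint.

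Four stronger readings are tempting but not supported:

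- A reader might infer that survival is not collected after a patient leaves against medical advice. That situation appears only under unblinding. No text calls it withdrawal or ends follow-up there, and the post-discharge calls could cover it. The text simply does not say.
- A reader might take the sentence on loss to follow-up as the error. It concerns patients who can no longer be reached, and using their data up to the loss is compatible with censoring in the planned Kaplan-Meier analysis. That censoring is informative only if leaving relates to prognosis.
- A reader might infer that patients who withdraw for an adverse event are followed for nothing else. The text does not say so, and a death while the event is being followed would be noticed.
- A reader might conclude that the endpoint is lost. It is not secured, which is a weaker statement.

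The criticism of the size also stands in part: the 30% is a planning allowance, and the bias figures come from chosen inputs.

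**Conclusion.** The point holds for withdrawal and for a stopped infusion: the stated rules do not secure day-28 vital status, and the exclusion can act only on the C-IVIG arm. For patients who leave against medical advice, the text needs to say whether the telephone follow-up applies. Because one stated analysis covers only those who finish the study period, following the text as written can lose deaths selectively, and it sits badly with the intention-to-treat statement.

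The scale is uncertain. Up to about 62 and 31 patients are exposed if the whole drop allowance becomes unknown survival. The illustrative bias is about 1 to 9 percentage points with no true effect, in either direction, resting on assumed leaving rates and leaver mortality and on an analysis of stayers only. Equal loss unrelated to prognosis would cause little bias. This is an improvement that should be made because it is cheap, not a flaw that by itself invalidates the design.

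**What to change.** In {18b} and {11b}, separate three events (stopping the infusion, leaving the hospital, withdrawing because of an adverse event) from a fourth: refusing further contact. Then:

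- Replace the exclusion clause in {11b} with continued outcome follow-up. When the infusion is stopped remains a clinical matter, and this change does not touch it.
- For every randomised patient who has not refused contact, including those who leave against medical advice, obtain vital status and any date of death at day 28 by telephone from the patient or a first-degree relative, identically in both arms.
- Record on the withdrawal form whether the day-28 call is accepted or refused.

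The cost is one tick box and at most about 93 extra calls (0.30×309 = 92.7, at one call each) by staff already assigned to follow-up. Patients who refuse contact will still have unknown survival.
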